### Secondary Outcomes

#### Child Health Behaviors

The effectiveness of HB4HNEKids on key preventative health behaviors including proportion of any breastfeeding at 4, 6, and 12 months old; age of introduction to solids; mean daily serves of vegetables, fruit, and discretionary foods at 12 and 24 months old; and child immunization rates will be assessed using validated items via computer assisted telephone surveys or online surveys (as part of the GFK Parent Collective or using service delivery data) sent out to program participants via a link. The data collected as part of the GFK Parent Collective will not be included within the individual child electronic medical records; however, the data will support the evaluation of this trial and support future health service planning through the ongoing development of the program and informing New South Wales Health services (eg, CFHS).

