##### Parents

The mHealth SMS text message program, HB4HNEKids, will be delivered to eligible parents or carers (from herein named parents) alongside usual face-to-face CFHS care. Parent eligibility criteria for both the intervention and control arms were developed in partnership with CFHS clinical leads, and include: (1) must be eligible to access CFHS located in the HNELHD; (2) must own a mobile phone with SMS capability (96%) [34]; (3) must have a baby who has been discharged from a hospital in the last 8 weeks; (4) had a length of hospital stay less than 45 days; (5) absence of complex social issues resulting in the infant needing out of home care; and (6) baby was born ≥32 weeks of gestation. Furthermore, CFHS clinicians can use their clinical judgment to exclude families from the program at any time based on unforeseen personal circumstances. Over an 18-month intervention period, it is expected that approximately 15,000 parents (ie, 10,000 per year) who are referred to CFHS will be exposed to HB4HNEKids. All eligible parents who are referred to CFHS will be included in the sampling frame and analysis. While this RCT is planned to 24-month follow-up, there is scope to longitudinally follow this cohort across the first 2000 days (until their child is 5 years of age) to explore several outcomes of interest.

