### Data Collection Procedures and Measures: Primary Outcome

The primary trial outcome will be the reach and representativeness of the HB4HNEKids program at 4, 6, 12, and 18 months from the commencement of the scale-up phase. The reach of the program by the scale-up model (clinician-initiated vs system-initiated) will be explored. Reach will be defined as: the number of eligible parents that are receiving HB4HNEKids (assessed via project records) and the proportion of parents receiving the program, calculated by the number of eligible parents receiving HB4HNEKids (numerator), divided by the total number of parents eligible for the program (denominator), identified via electronic health service records.

Representativeness will be assessed by comparing the characteristics of the parents receiving HB4HNEKids via each scale-up model to those of the total sample of eligible parents or carers referred to CFHS during the 18-month trial period. Characteristics of eligible parents (collected via electronic health service records and “The Good for Kids Parent Collective”) include parental age, geographic location, highest level of education, employment status (before birth of child), first baby (yes or no), number of children, language spoken at home other than English, and Aboriginal and Torres Strait Islander status. Sample representativeness of parents receiving the HB4HNEKids program at baseline and those remaining engaged at 18 months from both scale-up models will be compared, as well as compared with characteristics representative of the wider Hunter New England population.

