### Analysis

Analyses of trial outcomes will be undertaken under an intention-to-treat framework. For assessment of reach of HB4HNEKids—the primary trial outcome—between-group differences will be assessed using mixed logistic regression to account for any potential sector–level clustering effects. The regression model will include fixed effects for each arm of the trial and control for covariates prognostic of the outcome, including participant geographical location and ethnicity. To assess the impact of HB4HNEKids on child health behaviors, we will compare these outcomes between groups (clinician-initiated model vs system-initiated model) using mixed logistic and linear regression models. The model will include fixed effects for service and parent demographics that are found to be significantly different between scale-up models to account for potential consent bias. Subgroup analyses based on parent characteristics will also be conducted to examine differential effects on models of care against the outcome. We will use descriptive and comparative statistics to describe implementation and process outcomes, including engagement, acceptability, feasibility, appropriateness, and maintenance. All statistical tests will be 2-tailed with an α of .05.

Given that the trial is exploring the implications of the scale-up model (not the HB4HNEKids service), a data monitoring committee is not required for this trial. Data will be stored securely in accordance with the requirements of all ethics committees. Data will only be accessible to investigators listed on the ethics application and statisticians.

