## Discussion

### Principal Findings

Effective models for scaling up digital care to maximize reach and impact at the population level remain elusive. This research trial will compare 2 models (clinician-initiated opt-in vs automated opt-out) of scaling up an evidence-based SMS text message program delivered directly to parents during the first 2000 days. While both scale-up models will offer families the same SMS text messaging program (HB4HNEKids), the “opt-in” arm focuses on providing CFHS clinicians with targeted implementation support strategies to onboard eligible families, and the “opt-out” arm represents an automated “hands-off” approach, whereby families are automatically connected to the program using health service data. Given that the opt-in model is expected to require greater clinician-parent interaction in relation to the program, we hypothesize that the opt-in model will be most effective for improving health behaviors, while the opt-out program is expected to achieve greater reach and representativeness of program participants and be more cost-effective.

mHealth interventions (eg, SMS text messages) delivered directly to parents’ mobile phones present an opportunity to revolutionize the delivery of universal health care across the first 2000 days. Key international agencies recommend universal preventative health care across the first 2000 days as a critical initiative for improving population health outcomes, and scaling up such initiatives have been considered critical for attaining the United Nations Sustainable Development Goal [14,44,45]. However, a review of 14 obesity prevention interventions delivered to infants and young children indicated that only 1 study had been formally evaluated at scale [46], suggesting that methods of achieving effective scale-up are significantly lacking for this demographic, limiting potential population health gains. This research seeks to bridge this evidence-practice gap by testing 2 methods of scaling up HB4HNEKids that have been co-designed and assessed as suitable for scale-up according to the New South Wales Guide to scaling up [47].

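### On its natural reading, the child health behaviour survey goes to program recipients, so the between-arm comparison is conditional on enrolment and is not the intention-to-treat analysis the article states

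*Protocol article*

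**What the plan says.** Four parts of the protocol article bear on this point.

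- **Who is surveyed.** Under Child Health Behaviors, breastfeeding, introduction of solids, diet and immunisation are assessed by telephone or online survey, "as part of the GFK Parent Collective or using service delivery data", and the survey is "sent out to program participants via a link".
- **Who is to be analysed.** Under Parents: "All eligible parents who are referred to CFHS will be included in the sampling frame and analysis". Under Analysis: "Analyses of trial outcomes will be undertaken under an intention-to-treat framework".
- **How the arms are compared.** Also under Analysis: "we will compare these outcomes between groups (clinician-initiated model vs system-initiated model) using mixed logistic and linear regression models". The models adjust for service and for "parent demographics that are found to be significantly different between scale-up models to account for potential consent bias".
- **What is expected.** Receipt divided by eligibility is the primary outcome. The sample-size section assumes about 65% reach for opt-in and a detectable difference of 9.8 points. Principal Findings expects opt-out to do better on reach and representativeness, and on behaviours states that "we hypothesize that the opt-in model will be most effective for improving health behaviors".

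**The concern.** Whether a family receives the program is settled after its sector has been allocated, and the two models are built to settle it differently. In opt-in sectors, a family enters only after staff have made contact and it has accepted. In opt-out sectors, entry is automatic from referral data unless someone withdraws. If only recipients are surveyed, the two groups of respondents have passed through different filters, and randomisation no longer protects the comparison between them.

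Two things are at stake. First, a difference in breastfeeding, diet or immunisation could appear between arms when neither model has changed any behaviour. Second, the question a health service would ask at scale-up is which model leaves the eligible families of a sector better off. A recipients-only comparison leaves out the families a model failed to reach, and so does not answer it. Reporting the result as intention-to-treat would hide both problems.

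**Working it through.** **Step 1: the statements side by side.** Principal Findings, and Strengths and Limitations, use the term program participants for the families whose reach and representativeness are measured, that is, recipients. Read that way, the survey excludes eligible non-recipients. Parents and Analysis say that all eligible referred parents are analysed, by intention to treat. A survey of recipients cannot deliver that, and the article describes no route for surveying eligible non-recipients.

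**Step 2: inputs.** The article states no figure for bias in the behaviour outcomes, so there is nothing of its own to reproduce here.
- Opt-in reach: 65% (sample-size section).
- Opt-out reach: 65% + 9.8 = 74.8%, if opt-out is the higher arm. This is a detectable difference, not a forecast. A second value of 95% is my assumption, to show the range.
- Behaviour gap: 10 to 20 points, also an assumption.
- True effect of either model on behaviour: none.

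**Step 3: two simple selection models.**

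*Model A, the same gap d between recipients and non-recipients in both arms.* The recipient mean is the mean of all eligible families plus (1 − reach) × d. The opt-in minus opt-out difference is therefore (1 − r_in)d − (1 − r_out)d = (r_out − r_in)d.

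*Model B, nested.* Everyone reached by opt-in would also be reached by opt-out. The gap is the behaviour rate in families reached by both models minus the rate in families reached only by opt-out. The difference is ((r_out − r_in) / r_out) × gap.

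| Opt-out reach | Model | Factor | Gap 10 | Gap 20 |
|---|---|---|---|---|
| 74.8% | A | 0.748 − 0.65 = 0.098 | 1.0 | 2.0 |
| 74.8% | B | 0.098 / 0.748 = 0.131 | 1.3 | 2.6 |
| 95% (assumed) | A | 0.95 − 0.65 = 0.30 | 3.0 | 6.0 |
| 95% (assumed) | B | 0.30 / 0.95 = 0.316 | 3.2 | 6.3 |

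Entries are percentage points of spurious opt-in advantage. If the gap is negative, every sign reverses. Comparing all eligible families by allocated arm gives zero in every row.

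**Step 4: effect on the test, for illustration.** Take Model B, 1000 respondents per arm (assumed), a base rate of 43% (the article's national figure for any breast milk at 12 months) and no clustering. For gaps of 10 and 20 points, the chance of a significant difference when there is no effect is 9% and 22% at 74.8% reach, and 30% and 82% at 95% reach, against a nominal 5%. Allowing for sector clustering would widen the standard errors and lower these rates. It would not remove the bias.

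**Step 5: no selection at all.** Suppose receipt raises a behaviour by 5 points in either arm and non-recipients gain nothing. The benefit over all eligible families is 0.65 × 5 = 3.25 points under opt-in and 0.748 × 5 = 3.74 under opt-out, a difference of 0.49 in favour of opt-out. The recipients-only difference is zero. The two analyses answer different questions even without bias.

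**The case against.** **Coverage may be wider than recipients.** The article lists "Characteristics of eligible parents (collected via electronic health service records and “The Good for Kids Parent Collective" as a source for eligible parents, and the same Collective is the survey vehicle. Service delivery data are also named and need not stop at recipients, immunisation above all. The word participants is used loosely elsewhere, for families who have not yet been offered the program. This stands in part. A reader might infer that every behaviour is certainly measured in recipients only, and the text does not establish that. It still describes no survey of non-recipients, so the conflict remains.

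**The direction is not shown.** A reader might also infer that the design is biased towards the opt-in hypothesis. That requires families reached only by opt-out to have worse behaviours. It is plausible, because opt-in receipt needs contact and acceptance, but nothing in the article demonstrates it. This objection stands.

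**The size may be small.** The article gives no 95% opt-out reach and no gap of 10 to 20 points. Its nearest evidence is the pilot's 5% higher breastfeeding in participants than in families without the program. If all of that were selection, the bias would be 0.098 × 5 to 0.131 × 5, or about 0.5 to 0.7 points, at 74.8% reach, and 0.30 × 5 to 0.316 × 5, or about 1.5 to 1.6 points, at 95%. In addition, the arithmetic concerns recipients, while survey completion is voluntary. Less motivated opt-out families may not respond, which would narrow the gap. These are fair limits on the magnitude, not on the mechanism.

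**The authors foresee consent bias and adjust for it.** They do, and this deserves credit. But covariates picked by a significance test, and limited to service and demographics, cannot remove selection on motivation or service contact.

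**The outcomes are secondary, and a comparison among recipients is a legitimate question.** Both are true, provided the comparison is labelled as what it is.

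**Conclusion.** The point holds as an inconsistency with a real consequence. As written, the survey population does not match the stated analysis population, and the behaviour comparison is conditional on a post-randomisation event that is also the primary outcome. With no true effect and an assumed gap of 10 to 20 points, the bias is about 1.0 to 2.6 points at 65% against 74.8% reach, and about 3.0 to 6.3 points at an assumed 95% opt-out reach. It probably favours opt-in, but only on the undemonstrated condition that families reached solely by opt-out have worse behaviours. Otherwise it runs the other way.

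This should be fixed, but it does not threaten the trial's main result. Reach is counted from records over all eligible families, and the primary cost-effectiveness measure is based on reach. Neither is touched.

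**What to change.** 1. **Reconcile the text.** State in Parents, Child Health Behaviors and Analysis which families are surveyed, whether the Parent Collective includes eligible non-recipients, and which population each behaviour analysis uses. The cost is wording only.
2. **Immunisation.** Where service delivery data cover all eligible families, use them for everyone and analyse by allocated sector. This is analysis work on data the article already names.
3. **Survey outcomes: choose one route.**
   - *Survey regardless of enrolment.* Send the link to all eligible referred families in both arms, or to an equal random sample of them, and analyse by allocation. This needs an ethics amendment, and response among non-enrolled families is likely to be lower. Survey collection is projected to run to July 2027, so later waves could still be changed. Both arms work from the same type of maternity referral, so contact looks practicable, though that is an inference.
   - *Keep the participants-only comparison.* Weight respondents in each arm to that arm's eligible families, using characteristics held in records for all of them. Report the result as a non-randomised comparison conditional on enrolment, not as intention-to-treat, and say that weighting leaves unmeasured selection in place. This costs analysis time only, and is also the fallback for waves already collected.

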#### Cost-Effectiveness

The costs, cost-effectiveness, and potential cost savings of the scale-up models will be undertaken from the health service perspective. Resources used for the clinician-initiated and system-initiated models will be assessed via project records (infrastructure, staff, and consumables). Direct costs include digital infrastructure and text messaging platform, labor (health promotion team and CFHS), cost to develop additional material, clinician training, and implementation support. The cost-effectiveness of the scale-up models will be compared with the primary cost-effectiveness outcome, being incremental cost per unit change (%) in reach.

#### Process and Implementation Outcomes

##### Engagement (intervention adoption)

Project records obtained from project databases (REDCap) and the text message platform will be used to assess parental engagement with HB4HNEKids. Engagement data will include the proportion of eligible parents who click through on external hyperlinks embedded into SMS text messages at 4, 6, 12, and 24 months post baby’s birth. Engagement will continue to be measured across the first 2000-day period and reported as part of a further phase of data collection.

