The pilot implementation study of the HB4HNEKids SMS text message program required clinicians to offer the program to families during their first contact with the CFHS (clinician-initiated model). Clinicians provide child health and development assistance and advice, and, where needed, refer patients to secondary services. Clinician-initiated onboarding may increase the salience of the offer of the HB4HNEKids program, resulting in increased engagement and improved impact on behavioral outcomes, particularly as CFHS is considered a trustworthy source for infant and child health information and support [25]. However, engagement with CFHS is fragmented, with only 83% (8638/10393) of families in 2022-2023 attending their 1- to 4-week health check and a significant reduction in use of services thereafter. Additionally, there are barriers that impede a clinician’s ability to enroll participants into digital health interventions (DHIs) like HB4HNEKids, such as a lack of training and education, a lack of time, and a concern for increased workload, competing priorities, as well as infrastructure and technological barriers [26]. A system-initiated model, relying upon an opt-out approach, whereby parents and families are automatically enrolled into digital health programs such as HB4HNEKids, via data and systems, may have the potential to facilitate the universal offering of DHIs to eligible parents, likely at much lower financial cost than developing implementation strategies that address clinician barriers to enrolling participants. Opt-out approaches have shown promise in increasing participation in DHIs internationally [27]. For instance, a study evaluating a maternal and child health SMS text message program in a study from New Zealand found that transitioning from an opt-in to an opt-out model resulted in an increase in enrollments but had no significant effect on withdrawal rates [27]. However, the retrospective study did not report on the acceptability of the opt-out model, nor its impact on behavioral outcomes or sustainability, highlighting the need for further research in understanding factors that influence opt-out approaches. While an opt-out approach may seem promising, offering a DHI that does not include clinician contact may result in less trustworthiness and salience of information, resulting in less engagement in the DHI [28,29]. The effects of such models may also differ by participant characteristics that have the potential to drive inequity [30]. Although opt-out approaches have demonstrated potential in enhancing the reach of DHIs, there is limited data comparing the effects of a clinician-initiated and system-initiated models of care on parent engagement, representativeness, retention, effectiveness, and cost-effectiveness in digital health programs. Therefore, it is necessary to understand the impact of both scale-up models on these outcomes to optimize the success of DHIs.

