The HB4HNEKids program aims to support improved health and developmental outcomes for families by targeting barriers and enablers to optimal preventative health behaviors including (1) breastfeeding and appropriate introduction of solids by providing guidelines and practical information and advice, as well as facilitating referral pathways, to support best-practice infant feeding; (2) child nutrition including guidelines and strategies to implement and address responsive feeding, family foods, reducing discretionary foods, and increasing healthy foods; (3) physical activity and small screen recreation by connecting families to evidence-based resources, credible content, and real-world strategies that facilitate daily activities; (4) child health and development according to age, stage-relevant child milestones, and pathways for more information and support; (5) parental well-being, targeting practical approaches to self-care, connections, and self-efficacy; and (6) immunization and primary health checks by prompting and reminding families about scheduled checks with CFHS or general practitioners.

SMS text message content was developed as part of a pilot project and optimized to be delivered across both experimental groups in this trial. SMS text messages are tailored to include the infant’s name and infant feeding status (breast, formula, or mixed feeding status). The content includes up to 147 SMS text messages to be delivered over a 24-month period, with more frequent SMS text messages in the first 3 months (approximately twice per week), and every 1-2 weeks for the remainder of the first 2000-day period (Figure 1). The intervention messages included behavior change techniques that were designed to be primarily delivered via SMS text messages. Supplementary content was optional and available to access via embedded links, which require internet access. Almost all SMS text messages included embedded web links to related evidence-based online content, including websites, factsheets, podcasts, and videos (refer to Figure 2 for an example message).

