#### Control: System-Initiated (Opt-Out) Model

The control was a system-initiated (opt-out) model. The selection of a system-initiated model was based on clinician feedback during the pilot phase and automates the connection of families to the program. This model requires minimal input from clinicians. As per existing health service procedures, health service data are generated when CFHS receives a discharge referral from public and private maternity services for a mother or baby following the birth of a baby to initiate usual care via CFHS. This health service data will be used to identify parents who meet the predefined eligibility criteria for the HB4HNEKids program and will also be used to initiate the commencement of program messages, resulting in families automatically receiving the program. Predefined eligibility criteria were developed with and approved by CFHS clinicians. Nonetheless, CFHS staff are encouraged to refer to the program content as a potential trigger for discussions when conducting usual care. As part of this model, clinicians may opt out families from the program if it is not considered appropriate. Families can also opt out themselves, using the established pathways that cease program delivery to a family (eg, via links provided in messages, via links on the program website, or directly through a request to CFHS staff).

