#### Sample Size and Power Calculation

For the primary outcome, a sample of 1126 participants or families per trial arm will enable a detectable difference of 9.8%, assuming the opt-in model will achieve approximately 65% reach at 18 months (based on previous pilot data [awaiting publication]) with 80% power, α of .05, and an intraclass correlation coefficient of 0.05. Given the sectors involved in the trial are estimated to account for 55% of births within the Hunter New England area, achieving this sample should be possible.

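### Engagement is measured over all eligible parents, so it equals reach times clicking among recipients and can favour opt-out even when its recipients click less

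*Protocol article*

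**What the plan says.** The Engagement (intervention adoption) section says that project databases and text platform records "will be used to assess parental engagement with HB4HNEKids". The measure it names is "the proportion of eligible parents who click through on external hyperlinks embedded into SMS text messages", taken at 4, 6, 12 and 24 months after the baby's birth.

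The Primary Outcome section treats eligible parents and receiving parents as different groups. Reach is "calculated by the number of eligible parents receiving HB4HNEKids (numerator), divided by the total number of parents eligible for the program (denominator"), at 4, 6, 12 and 18 months from the start of the scale-up phase.

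The protocol expects the two quantities to move in opposite directions. The Introduction warns that a program offered without clinician contact may be trusted less and be less salient, "resulting in less engagement in the DHI". The Principal Findings section hypothesises greater reach with opt-out. The Analysis section plans descriptive and comparative statistics on engagement. The program description adds that the SMS provider could not track read receipts, so clicks are the only objective engagement measure named.

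**The concern.** The Introduction lists parent engagement among the evidence gaps that motivate comparing the two models. Its question is about families who get the messages: do those enrolled automatically use them less than those enrolled by a clinician?

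The stated measure counts every eligible parent who was never sent a message as not engaged. An arm with higher reach gains on engagement for that reason alone. A process outcome that should add to the primary outcome therefore contains it as a factor. If opt-out raises reach and lowers clicking among recipients, as the protocol thinks possible, the two effects offset each other within one number. That number may then show no difference, or a difference in the opposite direction to the one among recipients.

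**Working it through.** The protocol gives no engagement figure to reproduce, so the check rests on the definition and on the protocol's reach values.

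**Inputs**
- Opt-in reach R_in = 65%, from Sample Size and Power Calculation: "assuming the opt-in model will achieve approximately 65% reach at 18 months".
- Opt-out reach R_out = 65% + 9.8 points = 74.8%. The 9.8 is the detectable difference in the same section, and the direction comes from the hypothesis in Principal Findings. It is a planning value, not a forecast.
- Click rates among recipients, c_in and c_out: the protocol gives none, so the values below are assumptions.

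**Identity**, for parents counted in the same window:

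clickers/eligible = (recipients/eligible) × (clickers/recipients) = R × c

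**Tie point.** The arms score equally when R_in × c_in = R_out × c_out, that is, when c_out/c_in = R_in/R_out. Opt-out scores higher whenever c_out/c_in is above that ratio. This needs no assumed click rate.

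| Opt-in reach | Opt-out reach | R_in/R_out | Relative deficit in clicking at the tie |
|---|---|---|---|
| 65% | 74.8% (protocol) | 0.869 | 13.1% |
| 70% (approximate pilot reach, Introduction) | 74.8% | 0.936 | 6.4% |
| 65% | 90% (assumed) | 0.722 | 27.8% |
| 65% | 95% (assumed) | 0.684 | 31.6% |
| 65% | 99% (assumed) | 0.657 | 34.3% |

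**Examples at 65% and 74.8% reach, with assumed click rates**
- Equal clicking, 40% in both arms: 0.65 × 0.40 = 26.0% and 0.748 × 0.40 = 29.9%. The whole gap is due to reach.
- 40% opt-in, 36% opt-out: 26.0% and 0.748 × 0.36 = 26.9%. Opt-out looks slightly more engaging although its recipients click 4 points less.
- 30% opt-in, 25% opt-out (a 16.7% relative deficit, beyond the tie): 0.65 × 0.30 = 19.5% and 0.748 × 0.25 = 18.7%. The direction is right, but a 5-point deficit shrinks to 0.8 points.

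**Can the recipient rate be recovered by dividing by reach?** Only roughly. Reach is timed from the start of scale-up and engagement from each baby's birth. The final time points also differ (18 and 24 months). The two planned proportions therefore do not describe the same parents in the same window.

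**The case against.** The strongest defence is that the all-eligible denominator is legitimate. The section heading equates engagement with adoption, the analysis is by intention to treat, and dividing by all eligible parents keeps the comparison as allocated. A recipient denominator conditions on something that happens after randomization and that the two models select for differently. All of this stands, and it is why the existing figure should be kept. It does not make that figure an answer to the Introduction's question about families enrolled without clinician contact.

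A second defence is that reach is reported anyway, so a reader can divide. That gives an approximation, but the differing clocks rule out an exact rate.

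Third, the section's list of engagement data is open-ended, and a fuller plan may hold further tabulations. That is possible, but the article names only this measure and calls it engagement. If eligible was loosely meant as receiving, the wording still needs correcting, because the Primary Outcome section gives the two words different meanings.

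Three stronger readings are tempting, and the document does not support them:
- A reader might infer that clicks to leave the program or open a survey count as engagement, since families can opt out "via links provided in messages" and surveys are also sent by link. Nothing says that such links are counted. The program description presents embedded links as routes to content: "Supplementary content was optional and available to access via embedded links, which require internet access".
- A reader might take the n=6 and n=4 in Ethical Considerations as numbers of families opting out. They read most naturally as how often the opt-out link was sent, so they cannot show that almost nobody leaves, or that an 18-month comparison would be of practically the same recipients.
- A reader might conclude that "those remaining engaged at 18 months" needs a measurement that the plan lacks. The engagement schedule runs on child age, while the primary outcome runs on trial time. At most, the phrase is loosely defined.

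**Conclusion.** The point holds for the denominator. As defined, engagement is reach times clicking among recipients. At the protocol's own planning values for reach, it favours opt-out for any relative deficit in recipient clicking below about 13%, and it understates larger deficits. The identity and the 0.869 ratio rest only on the stated definition and the 65% and 74.8% reach values. The size of the masked deficit depends on the reach gap: about 6% if opt-in reach is nearer 70%, and about 28% to 34% if opt-out reach is assumed to be 90% to 99%. The click rates in the examples are illustrations.

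The consequence is limited. Engagement is a process outcome, the primary reach analysis is unaffected, and child health behaviors and parent acceptability are assessed separately. But the trade-off between reach and engagement is part of the trial's rationale, and this measure alone can point the wrong way on it.

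**What to change.** Keep the all-eligible click proportion and describe it as the adoption measure that respects allocation. At each engagement time point, add the proportion clicking among parents actually sent messages in that window, with both counts by arm. Label this second figure descriptive, because recipients are selected differently by arm. State that the Introduction's question about engagement without clinician contact is read from the second figure alongside the first.

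The cost is an extra tabulation of platform and project records already planned for use, with no change to trial conduct. The downside is that the per-recipient figure is not a randomized comparison: a difference may reflect who was enrolled as well as how they were enrolled, and the report must say so.
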